#### Qualitative data

We will conduct interviews with participants that examine: (1) their existing daily habits, (2) how they make decisions about their finances and health, (3) their decisions regarding their ART medications, and (4) how the medication influences the way they spend their money. The audio recordings of these interviews will be transcribed verbatim and translated from Luganda into English and stored on a secure data transfer website. The data will be entered into the software Dedoose and we will develop a structured codebook to identify a priori identified and emerging themes [49]. As is standard with a directed content analysis, the initial set of themes will be informed by existing issues identified in the peer-reviewed literature, complemented by our collective experiences with ART adherence in resource-poor settings.

#### Data management

Existing clinic identifiers will be used as unique study identification numbers during data collection. Consent forms will bear the name and signatures of study participants, but all other information (such as viral load tests, MEMS cap readings etc.) will be recorded using these unique clinic identifiers. Tablets used for data collection by study coordinators will be protected by passwords. The study team in Uganda (one team leader, two lead interviewers, and three supporting team members) will be in charge of collecting all data and carrying out the intervention. The Uganda team will transfer data weekly through a secure web portal (Kiteworks). The study team based in the U.S. will design data collection instruments and protocols, monitor qualitative and quantitative data for quality, and conduct all data analyses. Paper copies of consent forms will be stored and locked at the Mildmay RAND office in Kampala, and access will be granted to only key personnel and the principal investigator (PI). Any published material will not contain information that can be used to identify participants. There is no formal data monitoring committee since the trial was deemed minimal risk, but data monitoring will occur through weekly checks by the study team in the U.S.

#### Handling missing data and attrition

Missing data has been a minor issue in our previous studies with the same study population and outcomes. Attrition has been well under 10% per year. However, when subjects drop out, we will fit multiple logistic regression models to assess whether this dropout is random. If it is not, we will construct nonresponse weights using a logistic regression that correct for dropouts by assigning weights to continuing subjects that are inversely proportional to the predicted probability of the subjects’ continuing to the time period in question. Analyses will incorporate design effects from this weighting in the calculation of standard errors and tests of significance. In addition, we will perform sensitivity tests regarding changes in outcomes when excluding those with missing observations to give a fully transparent picture of the data.

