### Randomization

Randomization in a 1:1:1 ratio will occur after participants are recruited but before they complete a baseline survey to ensure that group assignment does not influence the answers given. We will stratify random assignment by age (under 25 or over 25), sex, marital status (married/cohabiting or unmarried), low CD4 count (below 200 or above 200), and viral load (detectable or undetectable). Stratified randomization is achieved by generating a separate block for each combination of covariates after identifying which clients fall into each block. We will then randomize treatment assignment within each block. We will use the *randtreat* package in Stata15 for the randomization procedure.

All clients recruited will complete the baseline survey approximately 2–3 months after recruitment. The client will be informed of their assignment to either one of the two intervention arms or the control group after completing the baseline survey.

Participants cannot be blinded to their treatment status and neither can interviewers. Interviewers are not blinded to treatment status when they read a MEMS cap. The data analyst who will conduct the impact analysis will be blinded to treatment assignment.

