### Sample size and power

We have calculated the size of effects that our sample will be able to detect with 80% power (two-tailed test) with regard to outcomes at months 12 and 24, and 10% attrition every year (we observed 5% attrition over 20 months in our previous studies so this is a conservative estimate). For the primary outcome of viral suppression, we use a conservative estimate of 70% of clients in the control group showing suppression, based on discussions with the Mildmay team. Our sample size of 110 participants in each of the three arms (total *n* = 330) will be able to detect a 7 percentage point difference for joint comparison of T1 and T2 against the control group at month 12, and about an 8.5 percentage point difference between the two intervention arms (a subgroup analysis). The corresponding differences at month 24 are 8 and 9 percentage points, respectively. These are considered small effect sizes (Cohen’s *d* of between .15 and .185), which we will be able to detect. For adherence, in our previous study we observed mean adherence rates of ~75% as measured by MEMS caps. Our sample size of 110 in each of the intervention arms and the control group will provide sufficient power to detect about a 6.5 percentage point difference in mean adherence between the two intervention arms (combined) and the control group. To test for differences in adherence between the two intervention arms, our study is powered to detect about a 7.5 percentage point effect as measured by MEMS caps. Again, this means we will be able to detect small effects. The corresponding differences we will be able to detect at month 24 are about 7 and 8 percentage points, respectively. Our main econometric models will include covariates that will improve precision. Therefore, these minimum detectable effects reported above are likely upper bounds.

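### Nonresponse weights depend on a preliminary dropout check that has low power for small or moderate arm-specific dropout, which leaves the unadjusted models exposed to a modest bias

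*Protocol article*

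**What the plan says.** The protocol article's section on handling missing data and attrition sets out a two-step rule. When participants drop out, "we will fit multiple logistic regression models to assess whether this dropout is random". The correction depends on the answer: "If it is not, we will construct nonresponse weights using a logistic regression". The weights are inverse to the predicted probability of continuing. The section gives no criterion for calling dropout random and no list of predictors. It does not say whether arm, or arm-by-covariate terms, enter either model. For sensitivity, "we will perform sensitivity tests regarding changes in outcomes when excluding those with missing observations".

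The sample size section plans for "10% attrition every year" and calls this conservative, citing 5% over 20 months in earlier studies. The attrition section adds: "Attrition has been well under 10% per year".

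The data analysis section makes intention to treat primary and completers secondary. It names a main unadjusted and a main adjusted model for viral suppression (Eqs. 1 and 2) and a parallel pair for adherence (Eqs. 3 and 4). The adjusted models include baseline adherence and baseline viral suppression.

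**The concern.** A check on a few dozen dropouts can easily find nothing when dropout does differ by arm, and finding nothing does not show that dropout is random. Under the stated rule, that result decides that no weights are built. If nothing is imputed either, the intention-to-treat analysis of observed outcomes already leaves out clients with missing outcomes. Excluding those with missing observations then gives the same estimate again, so the sensitivity analysis cannot reveal attrition bias in the case where it is needed.

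A pattern that would matter is the loss of poorly adherent clients from the control arm, which receives no prizes. This would raise observed suppression and adherence among the remaining controls and pull the estimated incentive effect downward. If the loss were in an incentive arm, the sign would reverse.

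**Working it through.** **1. Dropout counts.** Inputs: 330 clients, 110 per arm, 10% attrition per year (sample size section); 1:1:1 allocation (randomization section).
- Month 12: 330 × 0.10 = 33.
- Month 24: 330 × (1 − 0.9²) = 330 × 0.19 = 62.7, about 63.
- At the earlier studies' 5% over 20 months: 330 × 0.05 = 16.5.

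The protocol gives no dropout count and no power for the check, so it has no figure of its own to reproduce here.

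**2. Power to see an arm gap in dropout.** Assumption: two-sided 5% test of two proportions, power = Φ[(d − 1.96·se₀)/se₁], with se₀ from the pooled rate and se₁ from the separate rates.

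Worked case: average dropout 10%, control 13.3% (n = 110), pooled incentive arms 8.3% (n = 220).
- se₀ = √[0.10 × 0.90 × (1/110 + 1/220)] = 0.0350
- se₁ = √[0.133 × 0.867/110 + 0.083 × 0.917/220] = 0.0374
- (0.05 − 1.96 × 0.0350)/0.0374 = −0.50, so power is about 31%.

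| Gap | 10% dropout: control vs pooled | 10%: arm vs arm | 19% dropout: control vs pooled | 19%: arm vs arm |
|---|---|---|---|---|
| 5 points | 31% | 23% | 20% | 15.5% |
| 8 points | 62% | 51% | 42% | 33% |
| 10 points | 79% | 70% | 58% | 47% |
| 15 points | 98% | 96% | 89% | 81% |

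**3. Power to see dropout tied to a baseline factor in one arm only.** Here the overall dropout rate is the same in every arm, and only its link to the baseline factor differs.
- Binary severity marker (assumed 40% prevalence), odds ratio 2-3 in one arm: an arm-by-marker test has 14-39% power.
- The same pattern at odds ratios 2-4: a global main-effects test (arm plus 10 covariates) has 7-16%.
- Baseline adherence as a continuous factor, control arm only, odds ratio 1.5-2 per SD: a global main-effects test also rejects in 7-16% of simulated trials.

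**4. Bias when no weights are built.** A direct calculation shows the mechanism. Assume suppression of 47.5% with the marker and 85% without, so the true rate is 0.4 × 0.475 + 0.6 × 0.85 = 70%, the protocol's control rate. At 19% dropout and odds ratio 2, control clients drop out at 25.5% with the marker and 14.6% without.
- Retained with marker: 0.4 × 0.745 = 0.298
- Retained without: 0.6 × 0.854 = 0.512
- Observed suppression: (0.298 × 0.475 + 0.512 × 0.85)/0.810 = 71.2%

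The control rate is therefore 1.2 points too high. At 10% dropout (13.8% and 7.4%), the same steps give 70.6%, or 0.6 points.

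The simulation version uses 330 clients, no true effect, outcome logit 0.95 + 0.8 × standardized baseline adherence, control-only dropout at odds ratio 1.5-2 per SD, and 2,000 trials per setting. Size of the downward bias in the unadjusted pooled risk difference under the conditional rule:

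| Dropout | Bias |
|---|---|
| 5% | 0.3-0.6 points |
| 10% | 0.6-1.1 points |
| 19% | 1.2-2.0 points |

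**5. What removes it.** At odds ratio 2 and 19% dropout, always weighting with main effects only leaves −1.99 points, against −1.97 under the conditional rule. Always weighting with arm-by-adherence terms brings the bias to about 0. The covariate-adjusted model without weights is within 0.2 points of no bias. The standard error of the weighted estimate rises by about 2-4%.

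**6. Scale.** At 19% dropout, the standard error of the unadjusted pooled difference is about √[0.7 × 0.3 × (1/89.1 + 1/178.2)] = 5.9 points. The largest bias above is about a third of that (2.0/5.9 = 0.34).

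**The case against.** The strongest reply is that the protocol already contains the remedy. Eq. 2 adjusts for baseline adherence, and under the assumptions used here it removes the bias without weights and with better precision. That stands for Eq. 2. It does not protect the unadjusted Eqs. 1 and 3, and Eq. 1 is also called a main model.

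A reader might infer that the check rarely detects arm-specific dropout of any kind. The documents do not support that: power is 47-79% for a 10-point gap and 81-98% for 15 points. The protocol also names no significance test, level or predictors, so the low figures for baseline-related dropout describe assumed versions of the check. Leaving predictors to an analysis plan is normal and is not criticized here.

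A reader might also infer that the condition alone causes the bias. Step 5 shows otherwise: removing it without the interaction term gains nothing in this scenario.

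Two further points stand. Past attrition was well below the planning value, and at 5% dropout the bias is about half a point. The mechanism is also plausible, not documented. Viral loads come from routine clinic records, so leaving the study need not lose them. Controls are encouraged to visit the study office for equal contact, and participants are paid for questionnaires. No passage reports control-specific dropout.

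**Conclusion.** The point holds in a limited form. The protocol fixes a rule in which a low-powered check decides whether attrition is corrected at all. When the check finds nothing and nothing is imputed, the stated sensitivity analysis adds no information. For control-only dropout tied to baseline adherence, the unadjusted suppression difference is exposed to about 0.3-0.6 points of bias at 5% dropout, 0.6-1.1 at 10% and 1.2-2.0 at 19%. Eq. 3 is exposed in the same way, but its bias was not sized.

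These figures assume a 5% test level, the predictors described above, odds ratios of 1.5-2 per SD and the outcome model shown. It would go too far to conclude that the trial's main results would be seriously biased: the adjusted suppression model largely removes bias from dropout tied to the covariates it contains. Neither that model nor the weights would address dropout driven by factors not recorded at baseline. The rule is worth changing because the change is cheap.

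**What to change.** Do not let the dropout check decide whether to correct.
- Always report the inverse-probability-weighted unadjusted estimate beside the unweighted one.
- Include arm, baseline adherence, baseline viral suppression and arm-by-baseline-adherence terms in the weight model. Without the interaction, this bias remains.
- State that interpretation relies on the covariate-adjusted model when dropout occurs.
- Keep the dropout regressions, but only to describe who left and from which arm.

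The cost is a change of wording, one extra model, and a standard error about 2-4% larger for the weighted estimate. No data collection changes.

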#### Cost-effectiveness analysis

We will assess the relative cost-effectiveness of the two different ways of implementing the lottery incentives using standard methodologies [50]. We will estimate an incremental cost-effectiveness ratio (ICER), which is the incremental cost of the interventions divided by the incremental effectiveness of the interventions, for both primary outcomes:
6$$ \mathrm{ICER}=\left({c}_2-{c}_1\right)/\left({e}_2-{e}_1\right) $$

where *c*_*i*_ is the per capita cost of the respective treatment group (1 or 2) and *e*_*i*_ is the number of participants with viral suppression or high adherence in the treatment group. The numerator is the incremental cost of T2 relative to T1, that is the cost of incentivizing the measured adherence relative to incentivizing the viral load (mostly the cost of the MEMS caps). The denominator is the number of additional people with an undetectable viral load or high adherence in T2 relative to T1. We will estimate confidence intervals for our ICERs using the upper and lower ends of the confidence intervals of our estimated effect sizes.

We will use a micro-costing approach to the analysis, i.e., we will carefully track all costs associated with implementing each intervention. Fixed costs, such as clinic rental costs and overheads, will be allocated as the fraction of time the premises are occupied by study personnel during the intervention (i.e., the number of hours per week that a room is used for intervention purposes). Costs in the analysis will be assessed using a clinic perspective, taking into account all intervention costs but not costs that accrue to the participant. Since the interventions take place at the same time as scheduled clinic visits, we expect few (if any) additional costs to the clients. Also, it would be difficult to value costs incurred accurately given the wide variation in patients’ opportunity costs, for example.

We will differentiate between development costs and ongoing costs. Development costs include personnel costs for training needed to implement the interventions but will exclude costs that are associated purely with the research activities (e.g., surveys). The costs of MEMS caps will be included as intervention costs for T2 (which requires them for measuring adherence) but not for T1 (which uses the caps only for measuring outcomes for study purposes but does not rely on them for implementing the prize draws). The evolution of the running costs will be tracked carefully to ascertain whether there are cost efficiencies over time. Within those, we will differentiate between the fixed costs of the intervention and the marginal cost of adding an additional client, which will provide information on the generalizability of the interventions to other settings.

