##### Estimating impact on viral suppression

We will use a logistic regression to compare the likelihood of viral suppression between the three study arms after year 1 and after year 2. We will estimate an unadjusted model and a model that includes prespecified covariates to adjust for baseline characteristics and improve precision. We will adjust for the following covariates: age, education, sex, baseline adherence, baseline WHO disease stage, baseline viral suppression, duration on ART, self-reported physical health, self-reported mental health, and HIV disclosure status.

Our main unadjusted model has the following form:
1$$ \Pr \left({y}_i\right)=\mathrm{expit}\left({\beta}_0+{\beta}_1T{1}_i+{\beta}_2T{2}_i+{\epsilon}_i\right) $$

and our main adjusted model has the following form:
2$$ \Pr \left({y}_i\right)=\mathrm{expit}\left({\beta}_0+{\beta}_1T{1}_i+{\beta}_2T{2}_i+{\boldsymbol{X}}_{\boldsymbol{i}}{\boldsymbol{\beta}}_{\mathbf{3}}+{\epsilon}_i\right) $$

where *y*_*i*_ is the probability of viral suppression of individual *i*, T1 is an indicator for treatment group 1, T2 is an indicator for treatment group 2, and *ϵ*_*i*_ is the idiosyncratic error. The coefficients of interest are *β*_1_ and *β*_2_. Equation 2 has the term ***X***_***i***_***β***_**3**_, which includes a vector of the prespecified covariates described above (***X***_***i***_) and the respective coefficients (***β***_**3**_). We will estimate the marginal difference (or risk difference) between each of the three study arms as the following:
$$ \mathbbm{E}\left[{y}_i\right|T1=1\left]-\mathbbm{E}\left[{y}_i\right|\mathrm{Control}=1\right] $$: Impact of treatment 1 on the outcome relative to the control group$$ \mathbbm{E}\left[{y}_i\right|T2=1\left]-\mathbbm{E}\left[{y}_i\right|\mathrm{Control}=1\right] $$: Impact of treatment 2 on the outcome relative to the control group$$ \mathbbm{E}\left[{y}_i\right|T2=1\left]-\mathbbm{E}\left[{y}_i\right|T1=1\right] $$: Impact of rewarding adherence relative to rewarding viral suppression

We will also estimate a model where we pool T1 and T2 (relative to the control group) to estimate the impact of lottery incentives more generally.

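### The ICER is defined as a per-capita cost difference over a headcount difference, and its interval rule breaks down when the T2–T1 effect interval spans zero

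*Protocol article*

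**What the plan says.** The section on cost-effectiveness analysis compares T2 with T1 through ICER = (c2 − c1)/(e2 − e1), for both primary outcomes. The cost term c_i "is the per capita cost of the respective treatment group (1 or 2", and the effect term e_i "is the number of participants with viral suppression or high adherence in the treatment group". The text then repeats the headcount reading: "The denominator is the number of additional people with an undetectable viral load or high adherence in T2 relative to T1".

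For uncertainty it gives one rule: "We will estimate confidence intervals for our ICERs using the upper and lower ends of the confidence intervals of our estimated effect sizes". It says nothing about an effect interval that contains zero.

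The effect sizes themselves are defined under the impact on viral suppression: "We will estimate the marginal difference (or risk difference) between each of the three study arms". That is a difference in proportions, not in counts.

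**The concern.** Two things look wrong.

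First, the numerator is per participant and the denominator is per arm. The quotient is then neither the cost per additional suppressed client nor any other standard quantity, and it shrinks as the arms grow. A raw headcount difference also responds to unequal retention. The interval limits would come from risk differences, so they would not even share a scale with the point estimate.

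Second, a ratio is not monotone in its denominator across zero. If the effect interval contains zero, the two plugged-in values have opposite signs and do not enclose the estimate.

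The protocol's Discussion says this analysis will help guide whether the added cost of the MEMS caps is worth paying. If T2 appears better, a ratio that is too small makes the costlier arm look like better value than it is.

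**Working it through.** **Inputs**
- Arm size: "Our sample size of 110 participants in each of the three arms" (Sample size and power).
- Attrition: "10% attrition every year" (same section). 110 × 0.9 = 99 at month 12; 110 × 0.9² ≈ 89 at month 24.
- Suppression: a "conservative estimate of 70% of clients in the control group showing suppression" (same section). Using 70% for T1 is an assumption, since T1 is an incentivised arm; 78% is shown as an alternative.
- T2–T1 difference d: the section's stated detectable differences, 8.5 points at month 12 and 9 points at month 24.
- Alpha: not stated; two-sided 0.05 assumed.
- Cost: no figures are given. C denotes the per-client cost difference c2 − c1, taken as positive and fixed.

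The protocol reports no ICER, so there is no figure to reproduce.

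**Step 1: units**
- Eq. 6 as defined, with n counted per arm: C/(n·d).
- Consistent units: C/d, which equals total cost over counts, (n·C)/(n·d).
- Ratio of consistent to literal: n, whatever C and d are.

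At d = 0.085:
- Consistent: C/0.085 = 11.76C per additional success.
- Literal, n = 110: C/(110 × 0.085) = C/9.35 = 0.107C, too small by a factor of 110.
- Literal, n = 99: C/(99 × 0.085) = C/8.415 = 0.119C, too small by a factor of 99.

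At month 24, with 89 counted, the factor is 89.

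**Step 2: sensitivity to retention**
Suppose both arms have 70% suppression, with 103 clients retained in one and 95 in the other (illustrative numbers). The headcount difference is 72.1 − 66.5 = 5.6 people from no effect at all. A true 8.5-point difference with 99 per arm gives 8.4 people.

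**Step 3: the interval rule**
For proportions p1 and p2 = p1 + d:
- SE = √{[p1(1 − p1) + p2(1 − p2)]/n}
- interval for d: d ± 1.96 × SE
- plugged-in ICER limits: C/lower and C/upper

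Everything here is on the proportion scale, so that estimate and limits are comparable.

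| p1 vs p2 | n per arm | Interval for d (points) | Plugged-in limits | Point estimate |
|---|---|---|---|---|
| 70% vs 78.5% | 110 | −3.0 to +20.0 | −33.3C, 5.0C | 11.76C |
| 70% vs 78.5% | 99 | −3.6 to +20.6 | −27.6C, 4.85C | 11.76C |
| 70% vs 79% | 89 | −3.7 to +21.7 | −26.8C, 4.6C | 11.1C |
| 70% vs 75% | 99 | −7.4 to +17.4 | −13.5C, 5.7C | 20C |

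For the second row, SE = √[(0.21 + 0.168775)/99] = 0.0619 and the half-width is 12.1 points.

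The point estimate falls outside in every row, and must do so. If lower < 0 < d < upper, then C/d > C/upper. If d is negative, C/d < C/lower.

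**Step 4: how often the interval spans zero**
P = Φ(1.96 − d/SE) − Φ(−1.96 − d/SE):
- 70% vs 78.5%, n = 99: 0.72
- 70% vs 79%, n = 89: 0.72
- 70% vs 78.5%, n = 110: 0.70
- 78% vs 86.5%, n = 99: 0.65
- no true difference: 0.95

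**The case against.** The strongest defence is that the definition is loosely worded and would not be followed literally. The same section describes the numerator more generally as the incremental cost of T2 relative to T1, and total cost over headcount would be coherent. It also refers to standard methodologies, and the risk difference planned elsewhere is the natural partner of a per-capita cost. This stands to a degree: analysts may well compute the right quantity. But the explicit definition of c_i is per capita, the headcount is stated twice, and a general reference does not override a stated formula.

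A reader might infer that a published ICER is wrong by two orders of magnitude. The document does not support that: it reports no ICER, and the error arises only if Eq. 6 is applied as written. Nor is 110 a fixed factor; it is the full-arm value.

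The frequency in Step 4 is also open to challenge. It is unadjusted, whereas the plan adds covariates that it expects to improve precision. It also implies roughly 28% power at differences for which the plan claims 80%. Taken at face value, the plan's 80% would mean an interval spanning zero about 20% of the time. The simple two-proportion calculation does not reproduce that claim, which is a separate matter. Either way the rule fails whenever zero is inside the interval, and the Discussion names equal effectiveness of the two arms as a question to be tested, where that outcome is the expected one.

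A reader might also extend the frequency to the adherence ICER. Only viral suppression was examined, so that is not supported.

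Ignoring uncertainty in cost looks minor, since the plan says the incremental cost is mostly the caps.

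**Conclusion.** The point holds as a faulty definition and a faulty interval rule in a supporting economic analysis.

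The understatement equals the number of participants counted per arm and depends on no cost assumption. The failure of the interval when it spans zero is algebraic, given a positive cost difference. Its frequency, about 65–72% at the planned suppression differences, rests on the assumed T1 rate of 70% or 78%, the assumed alpha and an unadjusted comparison.

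It would be too strong to say that the ICER alone decides scale-up: the protocol says it will help guide that decision, alongside the comparison of effectiveness. It would also be wrong to infer any fault in the primary efficacy results from this point; randomisation, data collection and the outcome models do not depend on Eq. 6.

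**What to change.** Define e_i as the proportion of the arm with viral suppression (or high adherence), to match the per-capita cost and the risk difference. Alternatively, keep counts and use total arm costs over the same set of participants. State which participants form the denominator at each time point.

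Replace the interval rule with a method that treats cost and effect jointly: a participant-level bootstrap of cost and effect pairs shown on the cost-effectiveness plane, a Fieller interval, or net monetary benefit over a range of thresholds. When the effect may be near zero, net benefit or the plane is easier to read, because a Fieller set can be unbounded and percentiles of bootstrapped ratios inherit the same discontinuity.

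The cost is one corrected definition and a little more analysis of data already to be collected. No change to visits, sample size or primary analyses is needed.

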The Behavioral Economic Incentives to Support HIV Treatment Adherence study (BEST) is examining these various issues and will address the significant problem of low ART adherence and lack of viral suppression through giving lottery incentives to HIV clients. In BEST, viral loads are the biological endpoints of the intervention. The study is investigating two different models for implementing lottery incentives, and one arm is based only on measures readily available in the clinic. This arm does not rely on adherence measurement devices, has a low cost, and hence, is readily implementable in a real-life clinic context. The suitability of these two intervention arms for take-up will be further assessed by a cost-effectiveness analysis. BEST will also measure the persistence of effects for up to 12 months post-intervention to contribute much-needed empirical data to the lively debate on the longer-term effects of financial rewards once they are withdrawn.

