## Discussion

### Potential impact and significance of the study

Treatment adherence is critical to the success of ART and is largely determined by behavior. This study will test novel behavioral interventions to improve ART adherence and has the potential to enhance HIV treatment and prevention significantly. An increasing number of people have been on ART for many years (i.e., they are treatment-mature), and they may lack motivation to adhere to their medication consistently. This study will be one of the first that we are aware of that tests an intervention designed to increase the motivation of treatment-mature clients for adherence. The findings of this study will provide unique insight into the underlying behavioral mechanisms that affect HIV treatment adherence, which could be exploited to improve adherence in a variety of settings.

In addition, this study will test an intervention that is readily and cheaply scalable. While previous work by the study team has demonstrated that lotteries based on MEMS caps can be effective at encouraging adherence, this study will compare the efficacy of using measured adherence vs. viral load to determine lottery eligibility. While MEMS caps are relatively costly, viral load testing is now part of routine clinical care in Uganda and therefore, is available at no additional cost. We will test whether directly incentivizing viral suppression is as effective as incentivizing electronically measured adherence, and also conduct a cost-effectiveness analysis. This will help guide whether incentivizing viral suppression should be scaled up or whether the extra cost of the MEMS caps is worth the potential extra benefits of directly incentivizing adherence.

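### The planned cost-effectiveness ratio compares only T2 with T1, so by itself it cannot show whether either arm is worth adopting over usual care

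*Protocol article*

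**What the plan says.** The section on cost-effectiveness analysis states its scope first: "We will assess the relative cost-effectiveness of the two different ways of implementing the lottery incentives using standard methodologies". The discussion part of the Abstract likewise refers to two modes of implementation. Eq. 6 is then ICER = (c2 − c1)/(e2 − e1), to be formed for both primary outcomes. The cost index covers treatment groups 1 and 2 only. On the two parts of the ratio the text says "The numerator is the incremental cost of T2 relative to T1" and "The denominator is the number of additional people with an undetectable viral load or high adherence in T2 relative to T1". No ratio against the control arm is given.

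Two other places say what the analysis is for. The Background says: "The suitability of these two intervention arms for take-up will be further assessed by a cost-effectiveness analysis". The section on potential impact and significance, after raising whether T1 is as effective as T2, says: "This will help guide whether incentivizing viral suppression should be scaled up or whether the extra cost of the MEMS caps is worth" the possible added benefit of rewarding adherence directly.

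Effects against control are planned separately. The section on estimating impact on viral suppression lists, among its risk differences, "Impact of treatment 1 on the outcome relative to the control group", with the same for T2 and a pooled comparison. Costs are to be micro-costed for each intervention from the clinic's perspective, with MEMS caps charged to T2 but not to T1.

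**The concern.** A clinic deciding whether to take up a lottery has three options: T1, T2, or continuing as now. Eq. 6 orders only the first two. Its value is the same whether T1 gains a great deal over usual care or nothing, so it carries no information on whether T1 is worth paying for. If T1 turns out to have no effect, T2's proper comparator becomes usual care, and Eq. 6 then gives the wrong figure for T2 as well.

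What is at stake is the economic conclusion. The trial would have estimated what each arm achieves against control and what each arm costs, yet no planned quantity would state the cost of a gain over current practice. No primary outcome, sample size or error rate is affected.

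**Working it through.** The protocol states no ratio, no cost-effectiveness threshold and no unit costs beyond the prizes, so there is no figure to reproduce. The check is algebraic, with an illustration.

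**Algebra.** Write c0 and e0 for usual care, and read e as a proportion so that it matches the per-client cost (the text defines e as a number of participants).

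- Eq. 6: (c2 − c1)/(e2 − e1)
- T1 against usual care: (c1 − c0)/(e1 − e0)
- T2 against usual care: (c2 − c0)/(e2 − e0)

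Neither c0 nor e0 appears in Eq. 6, so its value cannot change with the control result. This holds for any inputs.

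**Illustration.** These inputs are assumptions: cost over usual care of USD 10 per client in T1 and USD 60 in T2 (so c0 = 0), and suppression of 75% in T1 and 80% in T2. Control suppression is varied around the 70% assumed in the section on sample size and power. Results are USD per additional suppressed client.

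| Control | Eq. 6 (T2 vs T1) | T1 vs usual care | T2 vs usual care |
|---|---|---|---|
| 60% | 50/0.05 = 1,000 | 10/0.15 = 67 | 60/0.20 = 300 |
| 70% | 50/0.05 = 1,000 | 10/0.05 = 200 | 60/0.10 = 600 |
| 75% | 50/0.05 = 1,000 | 10/0, undefined | 60/0.05 = 1,200 |

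In the last row T1 costs more than usual care for the same effect, so it is dominated and drops out. The relevant ratio for T2 is then 1,200, not 1,000.

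With assumed costs of USD 8 and USD 110 and the same suppression rates, Eq. 6 is 102/0.05 = 2,040 in every row. T1 against usual care is 8/0.15 = 53, 8/0.05 = 160 and undefined.

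**Text against text.** The relative scope in the cost-effectiveness section, the Abstract, and the second half of the significance sentence (is the extra cost of the caps worthwhile?) are all served by Eq. 6. The Background sentence on the suitability of the two arms for take-up, and the first half of the significance sentence on scaling up T1, are not served by Eq. 6 alone.

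**The case against.** The strongest reply is that the formula matches the scope its own section sets. That section and the Abstract describe a relative comparison of two modes, and the significance sentence, read to its end, offers T1 or T2 as the alternatives. The same section cites earlier work showing that MEMS-based lotteries can be effective, which explains the head-to-head focus. This stands: for the T1-or-T2 choice, Eq. 6 is the right ratio and should be kept. It does not cover the Background sentence, which sets no such limit and for which adopting neither arm is a live option.

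A reader might infer that an ineffective T1 could pass unnoticed and look efficient because it is cheap. The documents do not support that. The planned comparisons with control would show a T1 without effect, and the protocol claims only that the evidence will help with the scale-up decision, not that the ratio will be read alone.

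A reader might also infer that the planned analysis fails if the two arms perform alike. That too goes too far. With similar effects the cost difference itself favours the cheaper arm, subject to precision, and a denominator near zero is a weakness of any such ratio, including one against control.

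Finally, the article cites standard methods and condenses a fuller plan, so an unlisted ratio might simply be a detail left out. This has some weight, but here the article explicitly defines the ratio and confines its terms to groups 1 and 2.

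**Conclusion.** The point holds in a limited form. Eq. 6 answers which lottery design is the better buy. It cannot by itself answer whether either design is suitable for take-up, or whether T1 is worth scaling up. The effect estimates against control fill only part of the gap: they show whether an arm works, not what each gain costs.

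That Eq. 6 does not depend on the control result is exact. The dollar amounts above are illustrative and rest on assumed costs and suppression rates. The real ratios cannot be estimated from the protocol. Its prize values alone would not be enough, because they leave out the personnel, room and overhead costs that the analysis is to include. The consequence is confined to the economic analysis, and the change is an inexpensive improvement rather than the repair of a serious fault.

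**What to change.** Keep the T2 versus T1 ratio and add usual care as the reference option. Report T1 against control, T2 against control and T2 against T1, with the options ordered by cost and dominated options removed before the incremental ratios are read. Express cost as the per-client increment over usual care. Express effect as the estimated risk difference for suppression and, for the adherence ratio, as the difference in the proportion with high adherence.

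This needs no new data. Costs are already tracked for each intervention, all three arms are measured on both outcomes, and usual care carries no lottery cost. The work is two further ratios and a few lines of text.

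If the sponsor prefers to keep the head-to-head scope, the alternative is to reword the Background sentence on take-up and the significance sentence on scale-up so that both refer only to the choice between T1 and T2.
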